### Data collection and management

A database management system (in-house developed based on TeleForm® and MS-Access®) with components both on-site at the study center and at the data management center will be used for data collection and management. For the baseline and follow-up assessments at the participants' homes, an electronic case report form with programmed plausibility checks will be used to be completed offline and later uploaded to the database. Paper-based case report forms or documents (e.g. medical discharge questionnaires, training diaries, or process evaluation questionnaires) will be used in a machine-readable format and the collected data will be integrated into the database after verification. The on-site database management system includes automatic functions for reminding data collection and detecting missing or implausible data entries. This approach minimizes errors and missing data and ensures a high quality of data collection. Individual and identifiable information of the participants will only be stored in the on-site database as well as on encrypted local servers at the respective study site. Intercurrent events (falls, adverse events) in all groups will be collected by the physical therapists, entered on the telemedicine platform, and forwarded to the database manager via the telemedicine provider. All other data entries and contents of the telemedicine platform can be integrated into the database via the same path, if required. Only authorized study personnel and the external clinical monitor will have access to the database. All pseudonymized data will be collected at the data management center and the final data set will be accessible only to study personnel directly involved in the data analysis.

### Statistical analyses

A pairwise comparison of the primary study endpoints (SPPB and mRNLI at T1) will be performed. The comparison to the SPPB between conventional IG and CG will be analyzed in a confirmatory manner and considering the intention-to-treat principle. Further potential comparisons of these outcomes between the groups or time points or considering covariates will be evaluated exploratory using, for example, multivariate regression models. The secondary endpoints will be analyzed exploratory as group comparisons at T1 and T2 or over time using the appropriate statistical methods (e.g. statistical tests or multiple regression analyses further specified in a statistical analysis plan before analysis).

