The aim of this three-center study is to establish a three-month multimodal home-based intervention program following discharge from inpatient GR. The GeRas program *(“Geriatric Rehabilitation success”) *is a multi-professional intervention that includes individually adjusted progressive physical exercises, social counseling, and nutritional recommendation, initiated during the inpatient treatment and continued through a structured handover in the outpatient setting. The intervention will be delivered either conventionally by home visits and telephone calls (conventional intervention group, conventional IG) or based on an eHealth system by using tablet computers and a combination of home visits and video calls (tablet IG). The primary study aim is to evaluate the effectiveness of the GeRas program on the lower extremity function and, additionally, the social participation after three months. Secondary study aims will focus on the primary outcomes after six months, physical activity, frailty, concerns about falling, falls, movement-related self-efficacy, life-space mobility, nutritional status, health status, and health-related resource use. Furthermore, the costs and cost-effectiveness of the GeRas program will be analyzed, the tablet IG and the conventional IG compared, and barriers and facilitators for the implementation into routine care identified.

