### Components of the intervention program

The participants in both IGs will receive a three-month multimodal home-based intervention program that aims to improve mobility and to improve social participation. The GeRas program begins upon discharge from inpatient GR, ends after 13 weeks, and will be delivered by a multidisciplinary team consisting of physical therapists, geriatricians, and social workers employed at the discharging GR as well as social workers employed at the AOK Baden-Württemberg. Key components of the GeRas program are a) a physical exercise program, b) social counseling, c) person-environment fit, and d) nutrition advice. The exercise program and the nutrition counseling will be delivered by health-care professionals of the discharging GR, namely physical therapists and geriatricians, respectively. The social workers of the GR forward the participants’ social and care needs in detail to the social workers of the health insurance, who will render outpatient social counseling. Delivery of the program will be monitored by geriatricians, but the medical treatment will be left at the discretion of the participants’ primary care physician, who receives a detailed discharge report and records of the participants’ progress.

Participants’ mobility-dependent goals will be agreed at discharge from inpatient GR and both IGs will receive the same program content. Only the mode of delivery will differ between the two IGs.

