#### Primary outcomes

The primary outcome measures will be the physical capacity measured by the Short Physical Performance Battery (SPPB) and the social participation assessed by the modified Reintegration to Normal Living Index (mRNLI), 3 months after discharge (T1).

The SPPB is an objective assessment tool for evaluating lower extremity function in older persons including static balance, gait speed, and repeated chair rises [52]. It is considered a "gold standard" for evaluating exercise interventions in older persons, as the result is highly predictive for disability, rehospitalization, institutionalization, and mortality [57–60], and therefore a good indicator for future loss of autonomy.

The mRNLI is an instrument that incorporates social, psychological, and physical aspects and assesses patients’ perceptions of their ability to resume activities of daily living after a disabling illness or injury [47]. This 11-item questionnaire consists of two subscales. Information about regular activities, including questions about mobility, ability for self-care, daily activities, leisure activities, social activities, and family roles, is summarized in the subscale “Daily Functioning”. Interpersonal and intrapersonal behaviors, represented by questions on personal relationships, self-presentation, and general coping skills, are summarized in the subscale “Personal Integration”. All items of the mRNLI are rated on a 4-point Likert-scale (0 points = does not describe me or my situation; 1 point = sometimes describes me or my situation; 2 points = mostly describes me or my situation; 3 points = fully describes me or my situation). The mRNLI has demonstrated validity in studies of community integration of persons living with long-term consequences of chronic health conditions [61] and has been validated in pre-frail to frail older persons living in the community [62].

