### Randomization and blinding

Participants will be randomly assigned to one of the IGs or the CG using computer-generated block randomization with a 1:1:1 allocation ratio stratified by study site. The randomization will be performed by the Institute for Epidemiology and Medical Biometry of Ulm University, Ulm, Germany, using the randomization program ROM [69]. All assessments of primary and secondary outcomes will be performed by assessors blinded to group allocation. Data that reveal group allocation (e.g., training diaries) will be collected by the unblinded physical therapists prior to T1.

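### Two primary outcomes and a program delivered in two modes are declared, but only SPPB in the conventional IG is tested confirmatorily; a fixed sequence would close the gap at no alpha cost

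*Protocol article*

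**What the plan says.** **Primary outcomes.** The section of that name says "The primary outcome measures will be the physical capacity measured by the Short Physical Performance Battery (SPPB) and the social participation assessed by the" mRNLI, both at T1. The two are not ranked. The Abstract names the same pair, and Statistical analyses calls both of them primary endpoints.

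**Primary aim.** The Background says it is to "evaluate the effectiveness of the GeRas program on the lower extremity function and, additionally, the social participation after three months". It describes the program as delivered either conventionally or by tablet. Components of the intervention program adds that "both IGs will receive the same program content" and that only the mode of delivery differs. Comparing the two delivery modes with each other ("the tablet IG and the conventional IG compared") is listed separately, after the secondary aims.

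**Allocation.** Randomization and blinding specifies "computer-generated block randomization with a 1:1:1 allocation ratio stratified by study site", so 90 of the 270 participants go to the tablet IG.

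**Confirmatory test.** Statistical analyses says "The comparison to the SPPB between conventional IG and CG will be analyzed in a confirmatory manner and considering the intention-to-treat principle". It continues: "Further potential comparisons of these outcomes between the groups or time points or considering covariates will be evaluated exploratory". Sample size powers that same single comparison (SPPB change, conventional IG vs CG, 1 point, two-sided 5%, power above 80%). It gives no effect size, SD or power for mRNLI, and no separate power for the tablet IG.

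**The concern.** A primary outcome is normally one on which the trial intends to draw a confirmatory conclusion. Here mRNLI has the label without the test. The primary aim speaks of the GeRas program, which covers both delivery modes, while the confirmatory test covers one of them.

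However strong the data, the analysis as planned supports no confirmatory claim on social participation or on the tablet-delivered program. The Discussion nevertheless anticipates conclusions on both physical capacity and participation. A reader of the results could also take a nominally significant result on a declared primary outcome as confirmed when the plan gives it only exploratory status.

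This is not a gap left to an unseen analysis plan. The article itself assigns exploratory status to the remaining comparisons of the primary outcomes, and its reference to a later SAP is attached to the secondary endpoints.

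**Working it through.** **1. The plan's own figures.** Sample size deducts 10% and then 25% from 270: 270 × 0.90 × 0.75 = 182.25. The stated 182 reproduces, and it gives 182.25 / 3 = 60.75, about 60 to 61 per arm. The power claim cannot be fully reproduced because no SD is printed. With a 1-point difference and a two-sided 5% t-test, power reaches 80% only if the SD of SPPB change is at most about 1.94 (n = 60) to 1.96 (n = 61). The 80% used below is therefore an assumption in line with the plan's claim.

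**2. Labels against tests.** Counting each IG against CG on each declared primary outcome (my count; the article does not define this set):

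| Comparison with CG at T1 | Declared primary outcome | Status in Statistical analyses |
|---|---|---|
| SPPB, conventional IG | yes | confirmatory |
| mRNLI, conventional IG | yes | exploratory |
| SPPB, tablet IG | yes | exploratory |
| mRNLI, tablet IG | yes | exploratory |

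**3. Error rate of a fixed sequence.** Each step is tested at two-sided 5%, and only if all earlier steps were significant. A false rejection requires rejecting the first true null hypothesis in the order, and that test has level 5%. Family-wise error is therefore at most 5%. Simulation with three arms of 60, a shared control and outcome correlation 0, 0.3 and 0.6 agrees: 0.050 to 0.051 when all nulls are true, and about 0.05 when only the first is false and its effect is large. Step 1 is the present test at its present level, so its power does not change (0.80 in, 0.80 out).

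**4. Power of the later steps.** Assume 80% marginal power for every test (noncentrality 1.96 + 0.84 = 2.80) and correlation 0.5 between the two SPPB comparisons, which share the control arm.

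- *Tablet SPPB as step 2.* Both SPPB tests are significant with probability about 0.69 (0.698 at noncentrality 2.83).
- *mRNLI conventional as step 2, tablet SPPB as step 3.* With uncorrelated outcomes, the probability of confirming SPPB in both arms is 0.687 × 0.80 = 0.55. With outcome correlation 0.5 it is about 0.60.
- *In that second order,* step 2 itself succeeds with probability 0.64 (0.80 × 0.80, uncorrelated) to 0.70 (correlation 0.6). Step 4, mRNLI tablet, succeeds with probability 0.47 to 0.55.

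**5. Sensitivity to mRNLI power.** The article gives nothing from which to compute it. In the second order, with uncorrelated outcomes, tablet SPPB is confirmed with probability 0.687 × 0.50 = 0.34 if mRNLI power is 50%, and 0.687 × 0.30 = 0.21 if it is 30%. With outcome correlation 0.5 these become about 0.40 and 0.25.

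**The case against.** The strongest defense is that the plan is coherent. It powers one comparison and confirms that same comparison. With no planning values for mRNLI and no separate power for the tablet IG, confining confirmatory inference to the powered test is legitimate. The Background's wording also introduces participation as an addition, which hints that mRNLI ranks second. The tablet arm has other uses: the comparison of delivery modes, usability and the process evaluation. Exploratory analyses will still estimate all the effects. All of this stands, and it is why the existing test needs no change.

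It does not remove the mismatch. The Abstract, Primary outcomes and Statistical analyses all call mRNLI primary without qualification. The comparison of tablet with conventional delivery lies outside the primary aim, but tablet IG vs CG falls within the effectiveness of the program as the article defines it.

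Three stronger readings are tempting and not supported:

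- *Inflated type I error.* Unadjusted 5% tests would give a family-wise error of about 9-10% for two outcomes in one arm and 16-17% for all four comparisons. The plan rules that analysis out by calling the other comparisons exploratory.
- *A wasted tablet arm.* That 90 of 270 participants carry no confirmatory claim is a fact of the design, not an error in itself.
- *A free gain in conclusions.* The sequence costs no alpha, but it does not guarantee power for the later steps.

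**Conclusion.** The point holds as an inconsistency between the declared primaries and aim on one side and the confirmatory plan on the other. It is not an error-rate problem: the one confirmatory test is valid at 5%.

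The consequence is that no confirmatory statement is possible on mRNLI in either arm, or on the tablet-delivered program on either outcome, although a fixed sequence would permit such statements without loss to the existing test. How much would be gained depends on the order and on assumptions that the article does not supply. At 80% marginal power per test, SPPB is confirmed in both arms about 69-70% of the time with tablet SPPB second and about 55-60% with mRNLI second. The latter falls to about 34-40% if mRNLI power is 50%. The point deserves correction, but it does not threaten the validity of the planned primary test.

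**What to change.** Before unblinded analysis, the sponsor should choose one of two courses.

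1. **Fixed sequence.** Keep SPPB, conventional IG vs CG, as step 1 at two-sided 5%. Append mRNLI, conventional IG vs CG, and SPPB, tablet IG vs CG, then mRNLI, tablet IG vs CG. Each step is tested at two-sided 5% only if all earlier steps were significant, and results after the first failure are exploratory. The sponsor chooses the order of the appended steps, fixes it in advance, and states that the order affects power: placing mRNLI second makes a questionnaire with no stated power the gate to the tablet SPPB test.
2. **One confirmatory test.** Relabel mRNLI at T1 as a secondary outcome throughout, and restrict the confirmatory claim to SPPB in the conventional IG.

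The first course costs one paragraph, no alpha and no additional participants. The second costs consistent edits to the Abstract, aim, Table 2, Primary outcomes and Statistical analyses. Neither changes the existing test or its sample size.

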### Sample size

A power estimation was performed for the comparison of conventional IG vs. CG with differences in SPPB total score between T0b and T1. Information on changes within the control group and standard deviations is taken from a previous study [21]. A minimal clinically significant effect was defined as 1 point of the SPPB total score according to Perera et al. [68]. Assuming a recruitment of 90 participants in each study center will result in 270 participants in total within the recruitment period. At the study end, 182 participants (distributed among the three study groups) would be left for analyses after deducting 10% of participants due to a potentially higher variance in a multicenter design and an additional 25% due to the expected number of dropouts. This number of participants is sufficient to achieve a power of > 80% at a significance level of 5% using a 2-tailed *t*-test regarding the mentioned effect.

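### Power is computed for change in SPPB from T0b to T1, but the confirmatory test is worded as a comparison at T1 with covariates left exploratory, so the stated power above 80% does not automatically apply to it

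*Protocol article*

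**What the plan says.** The Sample size section of the protocol article defines the powered comparison: "A power estimation was performed for the comparison of conventional IG vs. CG with differences in SPPB total score between T0b and T1". On the inputs it says "Information on changes within the control group and standard deviations is taken from a previous study", without giving a figure, and "A minimal clinically significant effect was defined as 1 point of the SPPB total score". On numbers it says "Assuming a recruitment of 90 participants in each study center will result in 270 participants in total within the recruitment period". After a 10% deduction for multicentre variance and a further 25% for dropout, "182 participants (distributed among the three study groups) would be left for analyses". The claim is power above 80% at the 5% level with a two-tailed t-test.

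The Primary outcomes section defines the endpoints as SPPB and mRNLI at T1. The Statistical analyses section repeats this: "A pairwise comparison of the primary study endpoints (SPPB and mRNLI at T1) will be performed". It makes the SPPB comparison of conventional IG with CG confirmatory, under intention-to-treat, and continues: "Further potential comparisons of these outcomes between the groups or time points or considering covariates will be evaluated exploratory". The only mention of a statistical analysis plan in that section is attached to the secondary endpoints.

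Table 2 shows SPPB measured at T0b, T1 and T2. Randomization and blinding specifies "computer-generated block randomization with a 1:1:1 allocation ratio stratified by study site".

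**The concern.** A t-test on change and a t-test on the T1 value estimate the same treatment difference in a randomised trial, but with different variances. The power of one is therefore not the power of the other. The analysis section puts comparisons between time points, and those that use covariates, in the exploratory set. Change from T0b is a comparison between time points, and T0b SPPB and site are covariates. What remains as confirmatory is most naturally a plain group comparison of T1 scores.

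This goes beyond detail left to an analysis plan, because the article does assign a status to covariate-based analyses. A later plan that adjusted the confirmatory test would depart from this wording.

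At stake is the trial's only confirmatory test. If a patient's SPPB scores at T0b and T1 are strongly correlated, a raw T1 comparison could miss the 1-point effect although the baseline data that would sharpen it are already collected. The two descriptions also leave open which quantity decides the trial.

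**Working it through.** **1. The plan's own number.** 270 × 0.90 × 0.75 = 182.25, which reproduces the stated 182. Over three equal arms, 182 / 3 = 60.67 per arm.

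**2. What the stated power implies.** No SD is given, so the claim can only be solved backwards. With n = 60.67 per arm, a difference of 1 point, two-sided alpha 0.05 and the noncentral t distribution, power is 80% when the SD of the analysed quantity is 1.95. Power above 80% on change therefore requires an SD of change below about 1.95.

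**3. From change to T1.** Assume equal SDs at T0b and T1 and a correlation ρ between them. Then

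- SD(change)² = 2(1 − ρ) × SD(T1)², so SD(T1) = SD(change) / √(2(1 − ρ));
- residual SD after baseline adjustment = SD(T1) × √(1 − ρ²) = SD(change) × √((1 + ρ)/2).

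SD(T1) exceeds SD(change) when ρ > 0.5 and is smaller when ρ < 0.5. The adjusted SD is never larger than either.

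**4. Power for a 1-point difference, 60.67 per arm.** Both SDs of change and all values of ρ are assumptions. An SD of 1.95 is the limiting case. An SD of 1.5 is a favourable case, with 95% power on change.

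| ρ | SD(T1), if SD(change) = 1.95 | T1 unadjusted | Baseline-adjusted | SD(T1), if SD(change) = 1.5 | T1 unadjusted | Baseline-adjusted |
|---|---|---|---|---|---|---|
| 0.4 | 1.78 | 87% | 92% | 1.37 | 98% | 99% |
| 0.5 | 1.95 | 80% | 90% | 1.50 | 95% | 99% |
| 0.6 | 2.18 | 71% | 88% | 1.68 | 90% | 98% |
| 0.7 | 2.52 | 58% | 86% | 1.94 | 81% | 98% |
| 0.8 | 3.08 | 43% | 84% | 2.37 | 63% | 97% |

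**5. Where the unadjusted test falls below 80%.** Setting SD(T1) = 1.95 gives ρ = 1 − SD(change)² / (2 × 1.95²). This is ρ = 0.50 for an SD of change of 1.95, ρ = 0.60 for 1.75 and ρ = 0.70 for 1.5. Above those correlations the unadjusted T1 test has less than 80% power.

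The adjusted figures credit baseline SPPB only. Any gain from adding site depends on how far site predicts SPPB, for which the article gives no figure, so none is claimed.

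**The case against.** The strongest reply is that the article never calls the confirmatory test unadjusted and names no model for it. The exploratory sentence may describe additional analyses without restricting the confirmatory one. The only test named for conventional IG versus CG is the t-test on change in the Sample size section. The two sections could then be read together as a confirmatory t-test on change to T1, with no mismatch in power. That reading is possible, so the unadjusted T1 test is an inference and not a stated fact. It is still the more natural reading, because both the endpoint definition and the exploratory clause point to it. If the other reading is intended, the text needs to say so.

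A reader might also infer that the trial is underpowered. The document does not support that. It claims more than 80%, gives no SD, and does not say clearly whether the SDs from the previous study are of change or of scores. At correlation 0.4 the T1 test is more powerful than the test on change, and with an SD of change of 1.5 it keeps 80% up to a correlation of about 0.7. The figures from 43% to 71% belong to the limiting SD combined with correlations of 0.6 or more.

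The 10% deduction is an allowance for variance and not lost patients, so data may be available for 270 × 0.75 / 3 = 67.5 per arm. It may also already cover site variation in an analysis without site, so it is no evidence of inconsistency. At 67.5 per arm and an SD of change of 1.95, T1 power is still 75%, 63% and 46% at correlations 0.6, 0.7 and 0.8, so the dependence on the correlation remains.

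Finally, a randomised two-group comparison at T1 is valid without adjustment. That stands in full.

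**Conclusion.** The concern holds as a mismatch between the powered quantity and the confirmatory endpoint. As worded, the power above 80% belongs to a test on change, while the confirmatory comparison is most naturally a T1 comparison that uses neither T0b SPPB nor the stratification factor.

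The size of the effect on power cannot be fixed from the document. Over the assumed range (SD of change 1.5 to 1.95, correlation 0.4 to 0.8, equal SDs at both visits, 60.67 per arm, 1-point effect), unadjusted T1 power runs from 98% down to 43%. The adjusted analysis stays at about 84% or more. The protection that adjustment gives does not depend on knowing the correlation.

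The document does not support a definite loss of power, a biased estimate or an inflated Type I error. This should be fixed for efficiency and consistency, but it does not threaten the validity of the trial.

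**What to change.** Before unblinding, state one confirmatory analysis: a linear model of SPPB at T1 on arm, T0b SPPB and study site, testing conventional IG against CG two-sided at 5% under intention-to-treat. Restate the power for that model and report the SD and the baseline-to-T1 correlation used. The unadjusted T1 comparison can be kept as supportive.

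Recomputing the power with an SD at T1 and keeping the unadjusted test would also remove the contradiction, but it would leave the available precision unused.

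The cost is wording in the protocol and the analysis plan. T0b SPPB and site are already recorded, so no extra participants, visits or data are needed.
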